#### Secondary outcomes

Secondary outcomes will be analysed using either a t-test or Mann-Whitney U test for continuous data or a χ^2^ test for categorical data, as appropriate. Kaplan-Meier curves will be used to determine transplant-free survival. Kaplan-Meier curves will be used to determine the length of time for the subjects to reach the primary or secondary endpoint with regards to OHE. Censoring will be applied in analysis for liver transplantation or death by any cause. When censoring is applied, Cox proportional hazards model will be used. Comparison of peripheral and portal blood samples at TIPS placement will be analysed using a Wilcoxon signed rank test. Repeatedly measured endpoints will be analysed with mixed models, for the time point(s) they are measured (see table 1).

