### Statistical considerations

#### Sample size

The incidence of post-TIPS OHE is 20%–54% in international studies.^7–10^ To determine the incidence of new onset or worsening HE in our own population, we performed a retrospective analysis of the last 16 years of patients undergoing TIPS placement.^33^ This study revealed that approximately 33% of the patients suffered from new or worsening of existing HE within 30 days after TIPS placement. Between 30 and 90 days after TIPS placement, 17% still had HE. Actual percentages might be higher due to the retrospective nature of the study. Reduction of HE is achieved in 58% of the patients.^27^ However, due to selection bias, we estimate that in our study population. 50% reduction is realistic. The calculation of the sample size (nQuery Advisor V.7.0) was done for a χ^2^ test. Assuming that the effect of rifaximin and lactulose is a 50% reduction of HE, incidence of HE is expected to drop from 33% to 16.5%. With a two-sided 5% alpha, power of 80%, a total of 107 study subjects are needed in both groups. With an estimated dropout of 10%, a total of 119 study subjects are needed in the intervention group and 119 study subjects in the control group.

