#### Primary outcome measurement

The primary outcome, development of OHE within 3 months after TIPS placement determined by the West Haven criteria, will be compared between the intervention and placebo group. Percentage differences with corresponding 95% CI will be reported as absolute improvement in percentages.

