### Missing data

All efforts will be made to collect all data for each study subject to minimise missing data points. In the case of missing data, a multiple imputation approach will be applied, to be further detailed in the SAP.

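### Kaplan-Meier curves for time to OHE censor death and liver transplantation, which are competing events, so one minus Kaplan-Meier overstates OHE incidence; the censoring sentence also lacks a stated scope

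*Protocol article*

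**What the plan says.** All of the relevant text is in the protocol article, under Analysis of outcome measures.

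- **Primary outcome measurement.** OHE within 3 months is compared as a simple percentage: "Percentage differences with corresponding 95% CI will be reported as absolute improvement in percentages". No survival method is involved.
- **Secondary outcomes, first Kaplan-Meier analysis:** "Kaplan-Meier curves will be used to determine transplant-free survival".
- **Secondary outcomes, second Kaplan-Meier analysis:** curves to "determine the length of time for the subjects to reach the primary or secondary endpoint with regards to OHE".
- **Censoring rule, directly after the second analysis:** "Censoring will be applied in analysis for liver transplantation or death by any cause".
- **Model:** "When censoring is applied, Cox proportional hazards model will be used".

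The rule names no endpoint, transplant-free survival is not exempted, and no competing-risk method appears in the article. The Secondary objectives list transplant-free survival, OHE between 3 and 12 months, and time to OHE or minimal HE. A separate statistical analysis plan (SAP) is announced but is not at hand.

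**The concern.** A patient who dies can no longer develop OHE, and a patient who is transplanted leaves the condition under study. Kaplan-Meier with these patients censored treats them as if they could still have the event, at the same rate as those who remain. The resulting 1-KM describes a hypothetical population in which nobody dies or is transplanted, and even that only if censoring is independent of OHE risk. Independence is doubtful here. The Post-TIPS HE section names a higher Child-Pugh score and older age as possible risk factors for HE, and both plausibly drive death as well. The Economic evaluation section itself says that end-stage patients survive poorly or go on to transplantation.

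At stake is whether the OHE curves can be read as risks. If every patient is followed to 3 months, the proportion with OHE equals the cumulative incidence that allows for competing events. A Kaplan-Meier curve from the same patients would show a higher figure, so one report would carry two different 3-month OHE risks per arm.

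The second issue is scope. The censoring sentence follows two Kaplan-Meier analyses without saying which it governs, and for one of them death and transplantation are the events.

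**Working it through.** **1. The plan's own figure.** The Sample size section assumes that "incidence of HE is expected to drop from 33% to 16.5" per cent, and states: "With a two-sided 5% alpha, power of 80%, a total of 107 study subjects are needed in both groups". For a two-sided chi-square test with pooled variance and no continuity correction, with mean risk (0.33 + 0.165)/2 = 0.2475:

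n = [1.960 × √(2 × 0.2475 × 0.7525) + 0.842 × √(0.33 × 0.67 + 0.165 × 0.835)]² / 0.165²
= (1.196 + 0.504)² / 0.0272 ≈ 106.2, rounded up to 107 per arm.

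With 10% dropout, 107/0.9 = 118.9, rounded up to 119 per arm. Both stated figures reproduce. The calculation compares percentages, so the censoring rule does not enter it.

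**2. Inputs for the bias.**
- True OHE risk c: 33% (control) and 16.5% (intervention), the planning values in Sample size.
- Risk d of death or transplantation before OHE: **an assumption**, because the article gives none for this trial. I use 2% to 20%, the same in both arms. The only related figure is in Portal hypertension and TIPS: a cited trial with 93% one-year transplant-free survival after TIPS, hence 100% − 93% = 7% death or transplantation.
- Constant cause-specific hazards (assumption).

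**3. Formula.** The total cumulative hazard is H = −ln(1 − c − d). The OHE share is H × c/(c + d). With death and transplantation censored, 1-KM = 1 − exp[−H × c/(c + d)].

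Worked case, c = 0.33 and d = 0.07: H = −ln(0.60) = 0.511; OHE share = 0.511 × 0.33/0.40 = 0.421; 1-KM = 1 − exp(−0.421) = 34.4%.

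**4. Results at 3 months** (true values 33%, 16.5%, difference 16.5 points):

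| d | 1-KM control | 1-KM intervention | Difference (points) |
|---|---|---|---|
| 2% | 33.4% | 16.7% | 16.7 |
| 5% | 34.0% | 17.0% | 17.0 |
| 7% | 34.4% | 17.1% | 17.2 |
| 10% | 35.0% | 17.4% | 17.6 |
| 20% | 37.5% | 18.6% | 19.0 |

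Unequal competing risks shift the difference further: with d = 10% in control and 5% in intervention, 1-KM is 35.0% against 17.0%, a difference of 18.1 points before rounding.

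**5. Twelve months.** The article gives no 12-month OHE risk. If it were 40% (assumption), 1-KM would be 41.7% at d = 7%, 42.6% at 10%, 45.7% at 20% and 49.7% at 30%.

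**6. Scope of the sentence.** No arithmetic is needed. If death and transplantation were censored for transplant-free survival, no event would remain: the curve would stay at 100% and a Cox model could not be fitted. This follows only on the literal reading.

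**The case against.** Several points on the other side stand.

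- **Incidence is not planned to come from these curves.** The 3-month result is a difference in percentages, and categorical secondary outcomes are compared by chi-square. Kaplan-Meier is planned for time to OHE, and nothing says that 1-KM will be reported as the incidence. This limits the damage. A plotted curve will still be read as a risk over time, however, and it is the wrong one.
- **The Cox model is sound.** Censoring competing events is how a cause-specific hazard ratio is estimated. That comparison needs no replacement.
- **The bias may be small.** At 2% it is 0.4 points in the control arm. Using all of the cited trial's one-year 7% already at 3 months gives 1.4 points. MELD above 20 and emergency TIPS that cannot wait 72 hours are excluded. Against that, variceal bleeders with Child-Pugh C are eligible, so 7% is not an upper limit.
- **The article is only an outline.** Detail can be left to the SAP. But censoring death and transplantation is a rule that the article states, so the point does not rest on an omission.

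Three stronger readings are tempting but unsupported. A reader might infer that transplant-free survival will be analysed with no events. The censoring sentence comes directly after the OHE sentence and is most naturally limited to it, and the endpoint's name says what its events are. A reader might infer a 12-month overstatement of about ten points, but that needs 40% OHE and 30% death or transplantation, neither of which is in the article. A reader might also infer, from "In the case of missing data, a multiple imputation approach will be applied", that outcomes after death will be imputed. The article says nothing of values after death and defers the detail to the SAP, so no point is made of it.

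**Conclusion.** The point holds for the OHE curves. With death and transplantation censored, 1-KM exceeds the cumulative incidence of OHE whenever these events occur before OHE. For an assumed competing risk of 2% to 20%, the excess is about 0.4 to 4.5 points in the control arm and 0.2 to 2.1 points in the intervention arm. At the 7% borrowed from the cited trial it is about 1.4 and 0.6 points. These sizes rest on constant hazards, on the plan's 33% and 16.5%, and on competing rates that the article does not give. The direction does not depend on the rates. More bias is possible over 12 months, where competing events accumulate.

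For transplant-free survival there is an unclear sentence and no evidence that events will be dropped.

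The primary analysis, the sample size and the cause-specific hazard ratio stand as they are. Because only secondary endpoints are affected, this is a should-fix.

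**What to change.** In the SAP, and in the protocol if it is amended:

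1. Limit the censoring sentence to the time-to-event analyses of OHE and minimal HE.
2. State that death and liver transplantation are the events for transplant-free survival.
3. Replace the OHE Kaplan-Meier curves with Aalen-Johansen cumulative incidence by arm, with death and transplantation as competing events.
4. Keep the Cox model for the between-arm comparison, and label its result a cause-specific hazard ratio.

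The cost is a few sentences and standard software. Timing of OHE, death and transplantation is already needed for the planned analyses, so no new data are required. The change should be made before unblinding, so that the choice of estimator cannot appear to depend on the results.

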### Economic evaluation

On the condition that the outcomes of this trial show beneficial results, a cost-effectiveness analysis (CEA), cost-utility analysis (CUA) and budget impact analysis (BIA) will be performed. Costs per patient without post-TIPS HE and the costs per quality-adjusted life year (QALY) will be used as primary economic outcomes. The CEA will estimate costs per additional patient without post-TIPS HE, offset against cost savings associated with reduced incidence of post-TIPS HE by the use of rifaximin and lactulose for a short-term horizon (12 months). The CUA will estimate costs per additional QALY, with a horizon of 5 years. Analyses for the short-term horizon will be based on the empirical data from this trial. Observed differences in QALYs as well as resource use/costs will be extrapolated to 5 years evaluating medium-term consequences. A longer horizon is not reasonable, since patients with end-stage liver cirrhosis have a poor long-term survival or will be transplanted after further progression of disease. Resource use during admission(s) will be assessed by case report form, complemented with the institute for Medical Technology Assessment Medical Consumption Questionnaire, Productivity Costs Questionnaire and patients’ health records during follow-up. To estimate unit costs for observed volumes of resource use, Dutch reference prices will be used. Health state utilities to estimate QALYs will be derived from EQ-5D-5L measurements at baseline, after 12 weeks of treatment and 9 months after cessation of rifaximin and lactulose. Finally, a BIA from a governmental and health insurer perspective will be performed, describing the financial consequences of prophylactic use of rifaximin and lactulose and reduced number of hospital admissions for the extramural drugs budget respectively budget for specialised healthcare. The BIA will be performed in accordance to the Dutch guideline for economic evaluations in healthcare, using the international accepted International Society for Pharmacoeconomics and Outcomes Research (ISPOR) principles.

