**Methods and analysis:**

The Prevention of hepatic Encephalopathy by Administration of Rifaximin and Lactulose in patients with liver cirrhosis undergoing placement of a TIPS (PEARL) trial, is a multicentre randomised, double blind, placebo controlled trial. Patients undergoing covered TIPS placement are prescribed either rifaximin 550 mg two times per day and lactulose 25 mL two times per day (starting dose) or placebo 550 mg two times per day and lactulose 25 mL two times per day from 72 hours before and until 3 months after TIPS placement. Primary endpoint is the development of overt HE (OHE) within 3 months (according to West Haven criteria). Secondary endpoints include 90-day mortality; development of a second episode of OHE; time to development of episode(s) of OHE; development of minimal HE; molecular changes in peripheral and portal blood samples; quality of life and cost-effectiveness. The total sample size is 238 patients and recruitment period is 3 years in six hospitals in the Netherlands and one in Belgium.

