### Secondary objectives

To assess:

Ninety-day mortality.Transplant-free survival.The development of a second episode of OHE within the first 3 months after covered TIPS placement.The development of OHE between 3 and 12 months after covered TIPS placement.Time to development OHE or MHE episode(s).The change in PHES and S-ANT1 test during the study: at time points week 4, week 12 and week 52, compared with baseline.The change in Liver Frailty Index score at week 12 and week 52, compared with baseline.Differences in molecular composition of peripheral/portal blood samples at TIPS placement.Differences in molecular composition of peripheral blood samples at baseline, compared with day 10 post-TIPS, week 4, week 12 and week 52.Quality of life.Costs and cost-effectiveness.

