#### Secondary outcomes

Ninety-day mortality; development of a second episode of OHE within the first 3 months; development of OHE in the period between 3 and 12 months after covered TIPS placement; development of MHE between covered TIPS placement and 12 months after placement; time to development of OHE or MHE episodes; increase in the PHES, S-ANT1 score and LFI compared with baseline. Difference in the composition of portal blood samples, drawn at TIPS placement. TIPS placement data will be recorded. Furthermore, quality of life will be assessed by the Liver Disease Symptom Index V.2.0 (LDSI V.2.0) and EQ-5D-5L questionnaires. Costs will include costs of healthcare, productivity loss due to sick leave from work and out-of-pocket expenses.

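### Cost-effectiveness is declared as a secondary endpoint without condition, but its analysis is made to depend on an undefined favourable result

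*Protocol article*

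**What the plan says.** Three places in the protocol article declare the economic question without a condition. The abstract, under Methods and analysis, ends its list of secondary endpoints with "quality of life and cost-effectiveness". The Secondary objectives list includes "Costs and cost-effectiveness". The Secondary outcomes section adds "Costs will include costs of healthcare, productivity loss due to sick leave from work and out-of-pocket expenses".

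Data collection is also unconditional. Table 1 and the section on quality of life and economic evaluation questionnaires place EQ-5D-5L and the economic questionnaires at baseline, week 12 and week 52.

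The Economic evaluation section sets a different rule: "On the condition that the outcomes of this trial show beneficial results, a cost-effectiveness analysis (CEA". The same sentence puts the cost-utility (CUA) and budget impact (BIA) analyses under this rule. It does not say which outcome must be beneficial, or by what criterion. The section names the main economic outcomes: "Costs per patient without post-TIPS HE and the costs per quality-adjusted life year (QALY) will be used as primary economic outcomes". For the 12-month horizon it states: "Analyses for the short-term horizon will be based on the empirical data from this trial".

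**The concern.** An endpoint that is declared in advance should be analysed whatever the trial shows. Here, whether the cost-effectiveness endpoint is analysed depends on the trial's own result, and because the criterion is undefined, the decision can be taken after unblinding. That is result-dependent reporting of a secondary endpoint.

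The condition is also a poor one for an economic question. Cost per patient free of HE and cost per QALY depend jointly on costs and health effects. A trial that misses significance on OHE can still show that the strategy saves money, or that it clearly does not pay. Those are the situations in which a payer would want the analysis, and the rule may withhold it.

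A second consequence is selection. The data that decide whether the analysis is run also supply its 12-month estimates. Economic results that reach print would therefore come, on average over repeated trials, from trials with a larger observed benefit than the true one.

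**Working it through.** **1. The texts side by side**

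| Place in the protocol article | Status of the economic question |
|---|---|
| Abstract, secondary endpoints | cost-effectiveness listed, no condition |
| Secondary objectives | costs and cost-effectiveness listed, no condition |
| Secondary outcomes | costs listed, no condition |
| Table 1 and questionnaire section | data collected at baseline, week 12 and week 52, no condition |
| Economic evaluation | CEA, CUA and BIA run only if results are beneficial; term undefined |

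The first four rows and the last cannot all be followed after a trial judged not beneficial. This needs no arithmetic.

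**2. The plan's sample size, reproduced**

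Inputs from the Sample size section: control 33%, intervention 16.5%, two-sided alpha 5%, power 80%, χ² test, 10% dropout. Allocation is 1:1 (Randomisation section).

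- Mean proportion: (0.33 + 0.165)/2 = 0.2475.
- Variance term under the null: 2 × 0.2475 × 0.7525 = 0.3725, square root 0.6103.
- Variance term under the alternative: 0.33 × 0.67 + 0.165 × 0.835 = 0.3589, square root 0.5991.
- n = (1.960 × 0.6103 + 0.8416 × 0.5991)² / 0.165² = 106.2, so 107 per arm. Power at 107 is 80.3%.
- 107/0.9 = 118.9, so 119 per arm and 238 in total.

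The stated figures reproduce exactly. They are not in dispute and serve only to size the selection effect.

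**3. Selection if beneficial means p<0.05 in favour on OHE (an assumption)**

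Normal approximation at 33% vs 16.5%, 107 per arm:

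- SD of the observed difference: √(0.3589/107) = 0.0579.
- Smallest significant difference: 1.960 × √(0.3725/107) = 0.1156.
- Standardised cut: (0.1156 − 0.165)/0.0579 = −0.852, with φ = 0.2774 and probability of passing 0.803.
- Mean difference given a pass: 0.165 + 0.0579 × 0.2774/0.803 = 0.185. Ratio to the truth: 0.185/0.165 = 1.12.

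A binomial simulation (1,000,000 trials) agrees: 81.0% pass, with a mean difference of 0.1844 among those that do, a factor of 1.12. The share of trials with no economic analysis is therefore 19.0% by simulation and 19.7% by the normal approximation.

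**4. Selection if beneficial means only a difference in the right direction**

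In the same simulation 99.7% of trials pass, and the mean difference among them is 0.1655, against 0.165 for all trials: a factor of about 1.003.

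**5. Smaller true effects (assumed, not in the plan), significance gate**

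| True OHE rates | Trials with no economic analysis | Mean difference among those that pass | Factor |
|---|---|---|---|
| 33% vs 16.5% (design) | 19% | 18.4 points | 1.12 |
| 25% vs 12.5% | 34% | 15.4 points | 1.23 |
| 33% vs 23.1% | 63% | 16.2 points | 1.63 |

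**6. What cannot be computed**

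Every figure above concerns the OHE risk difference. The documents contain no unit costs, resource volumes, utilities or QALY values, so the effect on a cost-effectiveness ratio or on the budget impact cannot be derived.

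**The case against.** The strongest reply is that the size of the selection effect rests on a rule the article never states. It speaks of outcomes in the plural and names no test. Under the lenient reading the inflation is negligible, and a favourable but non-significant result might still open the gate. This stands, which is why both readings are shown and the significance gate is marked as an assumption. It also shows what the undefined word leaves open.

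A second reply is that the condition does not alter the estimator within this trial. That also stands. The inflation is an average over hypothetical trials that pass. Running the economic analysis after a neutral result would not change the estimate obtained after a positive one. Removing the condition cures selective reporting but does not shrink a fortunate estimate.

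Third, the loss is narrower than the whole objective. Only the three syntheses are conditional. Costs and quality of life remain secondary outcomes, and nothing in the article prevents their being reported by arm. This stands too: what is lost is the cost-effectiveness analysis itself.

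A reader might infer that the condition biases the cost-effectiveness result upward. The documents do not support that. No such bias can be computed from them, and the direction is easily misread: an overstated health effect would, all else equal, lower the cost per HE case avoided and the cost per QALY, and so flatter the value for money.

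A reader might also object to the 5-year step ("Observed differences in QALYs as well as resource use/costs will be extrapolated to 5 years evaluating medium-term consequences") because treatment ends 3 months after TIPS. The article does not say that a constant difference is carried forward. The choice of extrapolation model is a modelling preference that an article may leave to fuller documents, so it is no part of this point.

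The appeal to fuller documents does not remove the contradiction, because the article states the condition outright and it conflicts with the article's own lists of endpoints and objectives.

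**Conclusion.** The contradiction is established from the text alone. Cost-effectiveness is a declared secondary endpoint and objective without a condition, and its data are to be collected regardless, yet its analysis depends on a result that is not defined. Followed as written, a neutral or unfavourable trial could leave that endpoint unanalysed.

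The numerical consequence depends on an assumption. At the design rates with 107 per arm, a significance gate on OHE gives an average overstatement of the OHE difference of about 12% among trials that proceed, and no economic analysis in about 19–20% of trials. A direction-only gate gives about 0.3% overstatement. The first two figures grow if the true effect is smaller than planned. They describe selection across hypothetical trials, not an error in the estimator. The primary analysis and its conclusion are unaffected. The point deserves correction but does not threaten the trial's main result.

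**What to change.** In the Economic evaluation section, delete the condition for the cost-effectiveness and cost-utility analyses, and state that both will be performed and reported with their uncertainty whatever the primary result. Only the budget impact analysis may stay conditional. If it does, define beneficial before unblinding by naming the outcome and the criterion. The abstract and the Secondary objectives can then stand as they are.

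The cost is some extra analysis time after a neutral result. No extra data are needed, because the questionnaires are already scheduled for the trial.
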